### Power and sample size calculation

A sample size calculation has indicated that 500 patients per Health District would be sufficient to detect a 40% fall (15 to 9%) in relative IDC insertion rates with a power of 0.8 and alpha 0.05. This is based on a 50% (39.5 to 14.6%) reduction observed in the pilot study [34]. Estimated bed numbers of 860 in Health District 2 and 610 in Health District 1 should thus be more than adequate to provide sufficient power to detect a significant change. Further power will be obtained through having baseline control data and from stratifying the analysis by hospital wards.

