**Fig. 1 Fig1:**
[figure not shown]
Study Design. Data collection points are indicated with diamonds on timeline

Implementation of the intervention across four acute care hospitals will be staged, with multiple clusters in each of two implementation stages. Pre and post point prevalence data comparison will occur within all hospitals pre and post intervention, as well as between the two Health Districts as detailed in Fig. 1.

The staged implementation of the intervention allows for a control between the two Health Districts.

A mixed method design provides a platform to explore in-depth existing barriers and enablers related to implementing practice change. The sequential phased nature of the study ensures that the necessary evidence is available to inform the subsequent implementation phase of the study. The focus groups will identify barriers and enablers to implementation and uptake and will inform strategies to embed the intervention into normal practice. Questions in the focus groups will be informed by results from the point prevalence and clinician surveys.

The control will be usual urinary catheterisation practice, i.e., no intervention or implementation strategies. NSW Health evidence-based practice guidelines for “Adult Urethral Catheterisation for Acute Care Settings” [35], and local clinical practice guidelines for urinary catheterisation for each Health District are available for all clinicians, and can be accessed online.

The Clinical Excellence Commission (CEC), a corporation addressing patient safety and clinical quality in the NSW Health context, established a CAUTI project in 2014 to “help healthcare professionals in reducing the incidence of CAUTIs in acute care settings” [36]. A urinary catheterisation course on an online NSW Health learning platform also exists [37].

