### Exclusion and inclusion criteria

Point prevalence data will be collected from all adult inpatient wards across four hospitals in two Health Districts (excluding emergency departments, operating theatres and day only wards).

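### The 500 per Health District is an independent-patient figure with beds counted as patients, so 0.8 power is not established for the clustered between-district comparison

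*Protocol article*

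**What the plan says.** The section on power and sample size says that "500 patients per Health District would be sufficient to detect a 40% fall (15 to 9%) in relative IDC insertion rates". The target power is 0.8 and the significance level 0.05; sidedness is not stated. It moves from patients to beds: "Estimated bed numbers of 860 in Health District 2 and 610 in Health District 1 should thus be more than adequate". It adds: "Further power will be obtained through having baseline control data and from stratifying the analysis by hospital wards". No amount is attached to that gain, and no ICC, design effect, ward size or occupancy is given.

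The Design section describes a clustered rollout: "Implementation of the intervention across four acute care hospitals will be staged, with multiple clusters in each of two implementation stages". It also names the unit of control: "The staged implementation of the intervention allows for a control between the two Health Districts". The section on analysis of the point prevalence data plans two comparisons. One sets District 1 after implementation against District 2 before it has received the intervention. The other is pre against post within groups, and ward stratification is described there for the within-group data. The survey covers adult inpatient wards, "excluding emergency departments, operating theatres and day only wards".

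**The concern.** A sample size for independent patients has been attached to a study in which whole hospitals and districts change practice together. Patients on one ward share case mix, staff and catheter habits. The article itself gives variation in case mix between wards as its reason for stratifying. In a comparison of different wards in different districts, that correlation inflates the variance, and 500 patients carry less information than 500 independent ones.

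The adequacy claim then rests on total beds, whereas the data come only from eligible patients in occupied adult inpatient beds.

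The Background and Discussion present the controlled design as the advance over earlier uncontrolled pre-post work. If the stated power does not belong to the controlled comparison, a null result there could be misread as evidence of no effect. If the comparison were analysed on the same independence assumption as the calculation, its standard errors would be too small.

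**Working it through.** **Inputs from the protocol article.** Rates 15% and 9%; power 0.8; alpha 0.05 (two-sided assumed); 500 per district; 610 and 860 beds; hospital sizes 360 and 260 (District 1), 549 and 318 (District 2).

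**Assumptions, not in the documents.** 25 patients per ward; ward ICC from 0.01 to 0.05; 80% of beds filled by eligible patients as one occupancy example.

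**Step 1. Reproduce the 500.**

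n = [1.96·√(2·0.12·0.88) + 0.8416·√(0.15·0.85 + 0.09·0.91)]² / 0.06² = 459.3, so 460 per group.

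With continuity correction: (459.3/4)·[1 + √(1 + 4/(459.3·0.06))]² = 492 (493 if 460 is entered).

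The stated 500 is therefore the simple independent-patient figure, slightly rounded up. Power at 500 v 500 is 83% (81% with continuity correction). The arithmetic is sound; an allowance for clustering is absent.

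**Step 2. How much clustering can 500 absorb?** The largest design effect that keeps 80% is 500/460 = 1.09. With DE = 1 + (m − 1)·ICC and m = 25, this is ICC = 0.087/24, about 0.004.

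**Step 3. Power of the between-district comparison.** Sample sizes are divided by DE and power is recomputed by the normal approximation.

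| Ward ICC (assumed) | DE | 500 / 500 | All beds, 610 / 860 | 80% filled, 488 / 688 |
|---|---|---|---|---|
| 0 | 1.00 | 83% | 94% | 88% |
| 0.01 | 1.24 | 75% | 88% | 80% |
| 0.02 | 1.48 | 67% | 81% | 72% |
| 0.05 | 2.20 | 50% | 64% | 54% |

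With every bed filled, 80% power survives up to DE 1.53, a ward ICC of about 0.022.

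**Step 4. Beds as patients.** District 1 falls below 500 when fewer than 500/610 = 82% of its beds hold an eligible patient. Taken alone this matters little: at 70% fill (427 and 602) power for independent patients is still 83%. Its importance is that it uses up the slack that would otherwise absorb clustering, as the last two columns show.

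**Step 5. Hospital level.** Size-weighted hospital means are (360² + 260²)/620 = 318 and (549² + 318²)/867 = 464. With all beds filled, hospital ICCs of 0.001, 0.002 and 0.005 give power of 84%, 75% and 53%. This normal approximation is generous, since there are only two hospitals per arm. A difference between districts cannot be estimated at all from one district per arm, and more patients do not help.

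**Step 6. The within-district pre-post comparison.** I simulated 20 wards of 25 patients before and after (500 and 500), with a mean fall from 15% to 9%, a constant relative effect and no ward-by-time variation, and tested with a ward-stratified Mantel-Haenszel statistic. Power was about 84% at ward ICCs of 0, 0.02, 0.05 and 0.08. The same wards are compared with themselves, so stable ward differences largely cancel.

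**The case against.** The strongest reply is that the 500 may not be meant for the between-district comparison. It is given per Health District, it is worded as a fall, and it is modelled on a before-after reduction in the pilot. On that reading Step 6 applies, the stated 0.8 is met under its assumptions, and the remark on ward stratification is relevant. This stands for the pre-post contrast. It does not rescue the controlled contrast, because the article does not say which one the 500 serves and applies the adequacy claim without limit.

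It is also fair that full beds keep about 81% at a ward ICC of 0.02. A reader might infer that the study is certainly well below 80%; the documents do not support that, because they give no ICC, ward size or occupancy. Nor can a large ICC be derived from the prevalences in the Background. The 25% and 31% come from a urology and an orthopaedic ward in a pilot, while the 11% and 12.4% come from other studies in other hospitals. Together they do not estimate between-ward variance.

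A reader might also infer that the between-district model will omit ward and hospital. The article specifies no model, and such detail may sit in a fuller plan, so the risk of understated standard errors is conditional.

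The unquantified gain from baseline data does not settle the matter. An unadjusted difference-in-differences with independent patients has power of about 50% at 500 per district and 66% at 610 and 860.

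**Conclusion.** The concern holds for the between-district comparison. The stated sample size and power describe independent patients, while the article describes a clustered rollout with its control at district level. At 500 per district, 80% power is lost once the design effect passes 1.09. Over assumed ward ICCs of 0.01 to 0.05 with 25 patients per ward, power is 75% to 50% at 500 per district, 88% to 64% with every bed filled, and 80% to 54% at 80% fill. Variance between hospitals and districts comes on top. The size of the shortfall is conditional on these assumptions. What is firm is that the calculation does not support the power or the adequacy claim for the comparison that distinguishes this design. The ward-stratified pre-post comparison is not undermined in the same way.

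**What to change.** 1. State which contrast the 500 per district refers to.
2. For the between-district contrast, replace the sentence with a power or detectable-difference statement that includes a design effect. Estimate the ward ICC from the baseline survey before any post-implementation data are seen, and use the expected number of occupied eligible adult beds as n.
3. Account for ward and hospital clustering in the between-district analysis as well as the within-group one, and acknowledge that one district per arm leaves district differences inseparable from the intervention effect in the post-only comparison.
4. Remove the claim that bed numbers are ample, and either quantify or remove the claim of further power.

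The cost is rewording and one calculation from data the study already plans to collect. No extra patients are needed, since every adult inpatient bed is surveyed. The drawback is a less favourable stated power.

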### Statistical analysis – point prevalence data

Statistical analysis will be undertaken to determine differences in the prevalence of IDCs between Health District 1 (post) and Health District 2 (no intervention). A mixed methods analysis will compare pre and post data within the groups, across the time frame. Within group data will be stratified according to wards to allow for variation in the case mix of patients between wards. If differences in patient demographics are detected at baseline these will be controlled for in the between group analyses. Data linkage will be used to determine LoS and CAUTI rates for patients at each time point.

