### Setting

The intervention sites are four acute care hospitals from two Health Districts in NSW, Australia. Hospitals have been purposively selected, matched on total bed numbers, activity type and activity levels (See Table 1).

**Table 1 Tab1:** Setting

Health District	Facility	Beds
1	Hospital A	360
	Hospital B	260
	Total beds Health District 1 = 620	
2	Hospital C	549
	Hospital D	318
	Total beds Health District 2 = 867	

A key difference between the two health districts is the system used for medical health records: Health District 1 uses paper-based medical records, whereas Health District 2 uses electronic medical records. Data collection methods and training have been individualised to accommodate these differences.

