### Data collection

Three main types of data will be collected: Pre and post implementation point prevalence and patient demographics (quantitative) Pre and post implementation clinician knowledge and competence (quantitative) Post implementation perceived barriers and enablers to implementation (qualitative)

Data collection types and details are outlined in Table 2, and the data collection timepoints are displayed in Fig. 1.

**Table 2 Tab2:** Data collection sources and methods

Data	Data collection method	Data source(s)	Data collected	Data collection timepoint(s)
IDC usage rate and incidence of CAUTI	Online data collection tool	- Patient medical records – facility-wide across all four hospitals - Bedside observation - Infection control database	- Urinary catheter presence - Days catheter in situ - CAUTI rate	- Baseline - 4 months post-implementation commencement - 9 months post-implementation commencement
Patient profile	Data extraction and then merge with data from point prevalence	- Electronic patient management systems	- Patient demographics including age, gender, weight, diagnosis, type of admission	- Baseline - 4 months post-implementation commencement - 9 months post-implementation commencement
Clinician knowledge and competency	Online survey	- Clinicians (all nurses and medical officers invited from participating hospitals)	- Clinician competency - Clinician knowledge of CAUTI prevention - Perception of unit-based culture	- Baseline - 6 months post-implementation commencement
Barriers and enablers to implementation	Focus group	- Clinicians (6–8 per facility) (all nurses and medical officers invited from participating hospitals)	- Perceived barriers and enablers to implementation	- 6 months post-implementation commencement

The point prevalence data will be collected by project staff (clinical nurse consultants, research assistant), nurse and midwife clinicians and clinical nurse educators from each hospital. Training will be administered to all clinicians involved on data collection techniques and definitions prior to collection, and they will be paired where possible with members of the research team. Data collection staff will go to every inpatient bed on every adult inpatient ward in the hospital and input data into a firewall protected online survey tool. Survey data will then be exported and merged with other electronically extracted demographic patient data into statistical package STATA [38] for analysis.

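### The between-district comparison is adjusted for patient mix only if a difference is detected at baseline, which does not show that the patients actually compared are alike

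*Protocol article*

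**What the plan says.** The section on statistical analysis of the point prevalence data plans two kinds of comparison: catheter prevalence between District 1 (post) and District 2 (no intervention), and pre-post comparisons within groups.

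- Between districts, adjustment is conditional: "If differences in patient demographics are detected at baseline these will be controlled for in the between group analyses".
- Within groups, case mix is handled by design of the analysis: "Within group data will be stratified according to wards to allow for variation in the case mix of patients between wards".

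Other sections give the setting for these rules:

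- Selection (Setting): "Hospitals have been purposively selected, matched on total bed numbers, activity type and activity levels". There is no randomisation.
- Who is measured (Data collection): "Data collection staff will go to every inpatient bed on every adult inpatient ward in the hospital".
- When (Table 2): "Baseline - 4 months post-implementation commencement - 9 months post-implementation commencement".
- Covariates (Table 2, patient profile, at the same three times): "Patient demographics including age, gender, weight, diagnosis, type of admission".
- Power section: ward stratification appears once more, as a source of extra power.

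**The concern.** The trigger for adjustment examines one set of patients, while the comparison uses at least partly another. A survey of occupied beds in acute hospitals, repeated months later, will in practice find different people. Balance between districts at baseline therefore says little about the District 1 patients surveyed after implementation. Even for the baseline patients, failing to find a difference is weak evidence that none exists, and without randomisation balance cannot be presumed.

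The analysis section recognises that case mix varies between wards, yet states the ward remedy for within-group data only. The between-district rule mentions demographics alone.

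At stake is the between-district contrast, on which the study relies for its control of secular trends. If patients in the two districts differ in their underlying need for a catheter and the rule does not fire, that difference is read as an effect of the intervention, or hides one.

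**Working it through.** **1. The plan's own figure.** The power section says that "500 patients per Health District would be sufficient to detect a 40% fall (15 to 9%) in relative IDC insertion rates", with power 0.8 and alpha 0.05. For 15% v 9%, two-sided:

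n = [1.960·√(2·0.12·0.88) + 0.842·√(0.15·0.85 + 0.09·0.91)]² / 0.06² ≈ 460 per district; with continuity correction, 493.

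The stated 500 is reproduced, and the planned difference is 15 − 9 = 6 percentage points.

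**2. Inputs for the illustration.** From the protocol: 610 and 860 patients (the estimated bed numbers in the power section, taken as if every bed held a surveyed patient) and the 6-point target. Assumed, because the protocol gives no case-mix figures: surgical share 30% in District 1 and 35% in District 2; catheter prevalence 25% in surgical and 11% in other patients. These give 0.30·0.25 + 0.70·0.11 = 15.2% in District 1, close to the planning rate of 15%.

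**3. Chance that baseline detects the imbalance,** if detection means a two-sided 5% test:

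- Pooled share = (610·0.30 + 860·0.35)/1470 = 0.3293
- SE under no difference = √[0.3293·0.6707·(1/610 + 1/860)] = 0.02488
- SE under the difference = √[0.30·0.70/610 + 0.35·0.65/860] = 0.02467
- Power = 1 − Φ[(1.960·0.02488 − 0.05)/0.02467] = 0.52

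**4. Bias when the rule does not fire.** District 2 prevalence without any effect = 0.35·0.25 + 0.65·0.11 = 15.9%. The spurious difference is 15.9 − 15.2 = 0.7 points, and 0.7/6 = 12% of the target. Comparing 15.2% with 15.9% at these sizes and never adjusting gives a false-positive rate of about 6.5% in place of 5%.

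**5. The rule under several patterns of imbalance.** Simulation with 20,000 runs per scenario, 610 v 860 patients and no intervention effect. One binary risk factor is assumed, with a 30% share in District 2 and a lower share in District 1. Catheter risk ratio is 2 or 3 for that factor, with prevalence 15% in District 2. Adjustment is by Mantel-Haenszel.

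| District gap at baseline → at comparison | Rule fires | False-positive rate under the rule (RR 2; RR 3) | Always adjusted (RR 2; RR 3) |
|---|---|---|---|
| 0 → 0 points | 5% | 0.051; 0.050 | 0.051; 0.050 |
| 5 → 5 | about 56% | 0.054; 0.061 | 0.048; 0.049 |
| 10 → 10 | 99% | 0.050; 0.051 | 0.050; 0.050 |
| 3 → 10 | 24% | 0.081; 0.144 | 0.048; 0.050 |
| 0 → 10 | 5% | 0.090; 0.164 | 0.049; 0.053 |

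With a 10-point gap at the comparison survey, the unadjusted bias is 0.10·(0.2308 − 0.1154) = 1.2 points at risk ratio 2 and 0.10·(0.2813 − 0.0938) = 1.9 points at risk ratio 3. That is 19% to 31% of the target.

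**The case against.** Several points on the other side stand and limit the claim.

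- **A significance test is not named.** The text speaks of differences being detected, without a test or threshold. A reader might infer formal pre-testing and conclude that the confidence interval is invalid. The document does not support that, and the simulated error rates stay near 5% when imbalance is absent or stable. The 52% applies only if a 5% test is what is meant. The mismatch between baseline patients and compared patients does not depend on how differences are judged.
- **District 2's patients may be the baseline patients.** Table 2 lists no separate control survey, so the no-intervention data for District 2 could be its baseline survey. Fig. 1 would settle this and is not shown. The inference that different people are compared is safe only for District 1 (post).
- **The larger inflation needs a shift after baseline.** Nothing in the protocol shows a 10-point shift, and hospitals were matched on beds and activity. That matching is at hospital level, however, and does not balance the patients present on a survey day.
- **Ward stratification in the power section is not limited to within-group data.** It is offered there only as a source of power; the analysis section, which sets the method, confines it to within-group data.
- **Ward is not shown to be the strongest determinant of catheter use.** The Background gives 25% and 31% in two pilot wards against 11% and 12.4% in two hospital reports. The six-hospital survey implies 0.263·0.887 = 23.3%, so these figures do not isolate a ward effect.

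That detail may sit in an unseen analysis plan is no full answer, because the conditional rule is stated and is not merely left open.

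**Conclusion.** The point holds in a limited form. The stated rule can leave the between-district comparison confounded by case mix, because baseline findings do not establish the similarity of the patients compared and the ward remedy is stated only within groups.

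The demonstrated size is modest: 0.7 points, 12% of the planned difference, in an example whose case-mix inputs are all assumed. With a stable 5-point imbalance the false-positive rate is 0.054 to 0.061. It rises to 0.081 to 0.164 only if a 10-point gap at the comparison survey was small or absent at baseline. All the calculations treat patients as independent and use a single binary factor.

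A reader might go further and say that a shift after baseline is never corrected. That is too strong: the trigger still fires by chance in about 5% of balanced-baseline runs, and the planned pre-post analysis is stratified by ward. The case for change rests on a better rule being available at almost no cost, not on proof of large bias.

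**What to change.** Replace the conditional sentence with a prespecified adjustment set, applied in every between-district model whatever baseline shows: age, gender, diagnosis, type of admission and ward type. Use each patient's own values at the survey in which that patient was counted. Baseline characteristics can still be tabulated by district, but should not decide whether to adjust.

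The first four variables are listed in Table 2 for all three surveys. Ward type is not listed there, but should be recoverable because data are gathered ward by ward; the text should say that it is recorded.

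The cost is a sentence or two in the plan, slightly more analysis work and a few extra model parameters. In the scenarios simulated, always adjusting held the false-positive rate at about 0.05. The stated sample size is unaffected.

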### Qualitative analysis

All focus group interviews will be digitally audio-recorded and later transcribed verbatim by a professional transcriber/research assistant. Data will be analysed, coded and themed to low-level themes [44]. Cross-checking of coding will occur within the research team, and emerging themes will be shared within the whole research team as a check on credibility.

Using a mixed methods approach, the quantitative data from the point prevalence survey and the clinician survey will be analysed to inform the questions for the focus groups.

